#### Process evaluation

During the 10-week follow-up period, detailed qualitative data will be collected to assess acceptability, perceived usefulness, fidelity and implementation of the intervention, exploring in more depth what participants did and did not do and explanations of their actions, with questions similar to those shown above. Focus groups comprising the constellation of all school staff involved with one child will be held for all participants. This format is familiar to school staff as professional discussions often take a ‘case conference’ format. Interviews by phone or an online platform such as zoom will be conducted with a purposive sample of half of the parents, using the same criteria detailed above (ie, at least 50% from areas with a deprivation index above the regional mean) and aiming to attain a balance of male and female parents. Children will take part in ‘active interviews’ during the process evaluation in the follow-up period with a researcher (at home or at school), where they will have an informal conversation about their experiences of the study, if they recalled any new things their teacher tried with them, how they felt about their behaviour targets (if they knew about them), and how they found the research process.

All children will be invited to an activity- based interview with the option of a paired interview, where they can bring an accompanying family member of their choosing. Paired interviews can reduce stress, mitigate child protection risks and reduce issues of running a focus group where children in the school with traits of ADHD are identified to one another. The activity interviews will be designed with the planning group and piloted with children with ADHD, for example, these may involve collecting objects of different colours or taking photos around the school to represent answers to questions (such as *can you show me where you like to go if you feel you need to calm down? What are your favourite things about school? What do you not like about school?*), and using these objects or photos as prompts to discuss thoughts.

All participants in the process evaluation will be asked what they think the most important outcome would be for a future hypothetical trial of the toolkit, and why.

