### Recruitment and participants

Eight Primary schools, associated school staff and up to 32 children with impairing traits of ADHD (minimum 16 children) will participate in the study, and use the toolkit. All schools and all child participants will receive the intervention. Baseline data regarding treatment as usual will be collected in order to assess normal fluctuations in symptoms and response to any school-implemented treatment as usual during the baseline phase. Baseline data will not be used to exclude participants who have unstable profiles, rather to greater understand the nature of symptom and impairment fluctuation over time.

Recruitment will be through opportunistic sampling, using existing contacts from the planning group such as local Educational Psychology teams, and other education networks in the South West. At the time of writing, four schools have consented to participate and, given the demand for support managing children with ADHD in school, we anticipate no problems recruiting a total of eight schools. This sample of eight mainstream primary schools in the South West of England will allow sufficient variety to purposively sample schools to include a minimum of four in areas of high socioeconomic disadvantage, based on the selection of schools with an index of multiple deprivation above the regional mean. The intervention needs to be able to respond to the range of children with traits of ADHD, including those who are often unrecognised or less likely to access other support, such as girls,^28^ therefore eligible schools will have at least one female pupil meeting eligibility criteria and we will aim to recruit a diverse sample of children with differing ethnicities. A sample of eight schools also allows for the intervention periods to be staggered across the study and successive iterations of the toolkit. All participating schools will use the toolkit in the study for one school term.

Study participants include the school’s senior leadership or head teacher, who will consent to schools’ participation; the school special educational needs (and disabilities) coordinator (SENCo), teachers and teaching assistants (TAs) working with eligible children, eligible children with impairing traits of ADHD, and their parents. Consent will be obtained by a member of the research team through meeting with potential participants face to face or online.

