### Sample size

The planning group has advised that to minimise burden of data collection on teachers, each class teacher should have a maximum of one child participant however this may be revised during the course of the study; for example, if a school feels strongly that several children in one class may benefit, or if two eligible children in the same class also have TA support and the teacher wishes both to participate. Estimating that each of the eight participating schools will have 2–4 participating children and teachers, there will be a total of 16–32 child participants, 16–64 parents, and 16–64 teachers and TAs along with eight SENCos. The total sample size will depend on the distribution of participating parents, teachers and TAs and the distribution of eligible children across different classes within schools: table 1 indicates the minimum and maximum sample sizes.

**Table 1 T1:** Sample size minimum and maximum

Participant type	Minimum number	Maximum number*
School	6	8
Children	16	32
Parents or carers	16	64 (ie, 2 parents per child)
SENCos	8	8
Teachers	16	32
TAs	0	32

*Maximum number based on every eligible school recruiting four pupils, each of which have a different class teacher. We anticipate actual numbers of TAs will be lower than the maximum.

SENCo, special educational needs (and disabilities) coordinator; TA, teaching assistant.

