Given that the aim of the study is not to assess effectiveness or efficacy, the potential for the intervention to change between participants, and the case-series design, this study will not be powered to conduct a conventional between-individuals analysis. Instead, we will use multiple individual measurement points to analyse within-individual change and assess whether this replicates (at a descriptive level) across individuals. The pragmatic choice of eight schools allows for this purposive sampling, and both the minimum and maximum sample size of children is sufficient to address our objectives. Based on the mean number of children in eligible year groups in Devon schools, and a conservative estimate of prevalence of ADHD in this age group of approximately 3%, it is expected that each school will have four to eight eligible children, of whom we hope to recruit at least 50%. The recruitment target is feasible: school staff have indicated that a toolkit for ADHD would be perceived as useful and not burdensome as they believe it would be beneficial to their wider classroom management (the planning group highlight the data collection burden as being the reason that teachers should only have one participating student per class).

An established set of study progression criteria are shown in table 2 and will be used to assess success in terms of meeting the study aims. Criteria relate to the recruitment of schools (five or more being acceptable), recruitment of parents and teachers, and completion of study measures as well as some basic metrics of fidelity. The criteria will be reviewed throughout the study, and where individual criteria are Amber or Red, a core academics team meeting and a planning group meeting will be held to discuss, agree and then implement modifications to the study procedure or content.

**Table 2 T2:** Study progression criteria

	Green: acceptable	Amber: discuss, modify	Red: redesign	Assessing
Recruitment of schools	6 or more	5	4 or fewer	Feasibility
Recruitment: teachers, children, parents (considered as separate groups)	>65%	20%–65%	<20%	Feasibility
Retention of schools, teachers, children and parents in study	>65%	40%–65%	<40%	Feasibility
Training completed (teachers)	>90%	70%–90%	<70%	Acceptability and feasibility
Introductory video watched (parents)	>50%	20%–50%	<20%	Acceptability
Child strengths activity completed	>50%	20%–50%	<20%	Acceptability
Adherence to digital Daily Report Card	>70%	50%–70%	<50%	Acceptability

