#### Missing, unused and spurious data, and inclusion in analysis

All data will be used in analysis. Patterns of missing quantitative data will be evaluated as part of assessing the feasibility and acceptability of the intervention. Missing data could relate to the feasibility and acceptability of the intervention, or the utility and acceptability of the measure itself (i.e., Aim 1 and Subaim A), and so through the qualitative data collection we will aim to elicit how patterns of missing data relate to our aims and make modifications accordingly.

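### Follow-up parent interviews are sampled on deprivation and parent sex but not on engagement, so low-engaged parents may be under-represented where non-use and missing data are to be explained

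*Protocol article*

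**What the plan says.** The Process evaluation section of the protocol article states that parent interviews "will be conducted with a purposive sample of half of the parents". Two selection criteria are then given. The first concerns area deprivation, with parents chosen "using the same criteria detailed above (ie, at least 50% from areas with a deprivation index above the regional mean". The second concerns the sex of the parent, where the team is "aiming to attain a balance of male and female parents". The criteria that the section points back to are those for choosing schools: under Recruitment and participants, the plan is to "purposively sample schools to include a minimum of four in areas of high socioeconomic disadvantage". Neither section mentions toolkit use, form completion or withdrawal.

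The purpose is set in three places:
- Process evaluation: the follow-up data collection is for "exploring in more depth what participants did and did not do and explanations of their actions".
- Missing, unused and spurious data: "through the qualitative data collection we will aim to elicit how patterns of missing data relate to our aims".
- Subaim A: a measure counts as suitable only if its completion is green and the qualitative findings show no major barrier to repeated completion.

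Other provisions bear on the point. Under Toolkit iteration feedback, brief sessions are planned with all participating staff and parents during the intervention term. The analyses for Aims 1 and 2 use those sessions as well as the process evaluation. Aim 1 also judges acceptability quantitatively against Table 2, which includes "Introductory video watched (parents"), green above 50%.

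**The concern.** The sampling rule is stated in closed form: it is introduced with ie, not eg. It serves diversity of background, whereas the task given to the interviews is to explain differences in behaviour: who used the toolkit, who returned forms, and why others did not. Parents who agree to a follow-up interview may well be the more engaged ones, and nothing in the rule offsets that.

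Three uses of the interviews are exposed:
- **Suitability of parent measures.** Not hearing from non-completers makes it easier to find no major barrier. Green for parent-completed measures needs only more than 50%, so nearly half of the parent data could be missing when that judgement is made. The burden is not trivial: the Quantitative measures section has parents as well as teachers report the problem-behaviour subscale, and Table 3 schedules it 7 + 6 + 5 = 18 times over the three terms.
- **Reasons for missing parent data.** These are best known to the parents whose data are missing.
- **The future primary outcome.** Subaim A draws on views collected in the process evaluation, where parents' views come from the interviewed half.

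**Working it through.** No stated figure is in dispute. The check asks what the rule permits, and how far under-representation could go.

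**1. Number of interviews.** Sample size gives "there will be a total of 16–32 child participants, 16–64 parents, and 16–64 teachers and TAs". This reproduces: 8 schools × 2–4 children = 16–32 children; × 1–2 parents = 16–64 parents. Half is 8–32 interviews.

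**2. What the rule permits.** Take video viewing as the marker of engagement. The smallest number of watchers that is still green (>50%) is 9 of 16, 17 of 32 or 33 of 64. The interviews number 8, 16 and 32. An all-watcher sample is therefore possible at each size, provided the watchers include enough parents from deprived areas and of each sex. This shows possibility, not likelihood.

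**3. If selection is unrelated to engagement.** With N parents, k of them low-engaged, P(none interviewed) = C(N−k, N/2) / C(N, N/2).
- N = 16: k = 2, 3003/12870 = 0.233; k = 4, 495/12870 = 0.038; k = 7, 9/12870 = 0.001.
- N = 32: k = 4, 0.051; k = 8, 0.001.
- N = 64: k = 8, 0.002.

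A neutral draw would rarely miss them all unless they were few.

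**4. If engaged parents are w times as likely to be interviewed.** The values of k and w are assumptions. This was simulated as weighted sampling without replacement (100,000 draws), with k = 25% of parents:

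| w | P(none), N = 16 | P(none), N = 32 | P(none), N = 64 | Low-engaged share of interviews |
|---|---|---|---|---|
| 1 | 0.04 | 0.00 | 0.00 | 25% |
| 2 | 0.17 | 0.02 | 0.00 | about 17% |
| 5 | 0.46 | 0.20 | 0.04 | about 8% |
| 10 | 0.67 | 0.44 | 0.19 | about 5% |

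With k at about 44% of parents, the share falls to about 32%, 19% and 12% at w = 2, 5 and 10, and P(none) at N = 16 is 0.01, 0.12 and 0.31.

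**5. A milder worked case.** Take 32 parents, of whom 17 watched (17/32 = 53%, green) and 15 did not (47%). Assume that 80% of watchers and 30%–50% of non-watchers accept an interview. The non-watcher share is then:
- at 30%: 15 × 0.3 / (17 × 0.8 + 15 × 0.3) = 4.5/18.1 = 25%;
- at 50%: 15 × 0.5 / (17 × 0.8 + 15 × 0.5) = 7.5/21.1 = 36%.

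That is about 4 to 6 of 16 interviews, where proportionality would give 7.5. If all are invited, the chance that none of the 15 accepts is 0.7^15 = 0.005 at 30% and 0.5^15 = 0.00003 at 50%.

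**The case against.** The strongest reply is that the half-sample is an extra layer. Every participating parent is due feedback sessions in the intervention term, at two points in Table 3, and these ask about the measures as well as the toolkit. The missing-data section relies on qualitative data collection generally, not on the follow-up interviews alone. All staff around each child join a focus group, and all children are invited to interview. This largely stands: it rules out saying that missingness cannot be explained for those with missing data. It does not close the gap. The sessions are brief, fall before the follow-up term, and may be missed by the same parents who return no forms.

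A reader might also infer three stronger things, and the documents support none of them:
- *That acceptability will be overstated.* The Table 2 criteria do not depend on who is interviewed; a parent who skips the video lowers that criterion directly. Likewise, dropping the requirement for active parent engagement is raised under Aim 2 as something to discuss when criteria turn amber or red, so measured non-engagement triggers it.
- *That the criteria select against disengaged parents.* They are neutral on engagement; only differential willingness, which is assumed here, would tilt the sample.
- *That withdrawn parents are excluded.* The text sets no retention condition. It simply makes no provision for reaching them.

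Finally, the article is condensed and its supplement is not shown, so a finer sampling frame may exist. The criteria that the article does state still omit engagement. It is also fair that qualitative sampling seeks range rather than proportionality, but that is a reason to make engagement one of the ranges sampled.

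**Conclusion.** The point holds as a mismatch between sampling rule and purpose. Low-engaged parents may be under-represented in the follow-up interviews, so the explanations of parental non-use, barriers to measures and missing data may lean towards engaged parents. Under the assumptions shown, a 25% low-engaged group would supply about 5%–17% of interviews, and a 47% group about 25%–36%. Complete absence is a realistic prospect mainly near 16 parents with strongly unequal uptake; elsewhere the supported claim is under-representation. The uptake ratios and the size of the low-engaged group are assumptions, because the article gives neither. The quantitative acceptability assessment is untouched. This is an improvement to a stated design choice, not an error or contradiction in the protocol.

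**What to change.** Keep the number of interviews. Add engagement to deprivation and parent sex as a purposive criterion, defined from data the study already collects: video watched or not, proportion of parent forms returned, and withdrawal where the parent agrees to further contact. Require that both higher- and lower-engaged parents are included; a fixed quota is not needed. In the report, tabulate the engagement of interviewed against non-interviewed parents, so that readers can see whose explanations they are reading.

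The cost is a revised invitation list and one descriptive table. The downside is possibly lower interview uptake and fewer accounts from fully engaged parents. Because uptake feeds the Table 2 criterion for follow-up qualitative completion (green above 50% for each type of respondent), the plan should state whether its denominator for parents is all parents or those invited: interviewing exactly half of all parents gives 50%, which is not above 50%.

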#### Adverse effects of intervention

It is possible that the intervention will lead to adverse effects or negative impacts on participating children, such as feeling singled out due to the intervention leading to social exclusion from the peer group.^32^ The study planning group will contribute to identifying potential adverse effects (*as of 21 March social exclusion is the most prominent concern*), and qualitative data will be collected from participants at the feedback and process evaluation stages to assess perceptions of negative impacts of the intervention. Modifications will be made as needed in relation to this through consultation with the planning group and the academic advisory team.

### Quantitative measures

There are two quantitative outcome measures that will be assessed in order to: (1) Determine which would be most suitable as the primary outcome in a future trial and (2) Evaluate whether they make sense and are relevant to those completing the measures. *ADHD symptoms* will be measured using the Strengths and Weaknesses of ADHD Symptoms and Normal‐behavior Questionnaire, based on preferences of the planning group who considered several measures of ADHD symptoms,^33 34^ reported by teachers; and *classroom functioning problem behaviour* subscale measured using the Social Skills Improvement System (SSIS),^35^ that captures social, academic and competing problem behaviours in the classroom environment, reported by parents and teachers. These will be measured every 2 weeks during the baseline and intervention periods and every 3 weeks during the follow-up period. All planned quantitative measures are detailed in a table in the online supplemental material.

Other quantitative measures will be captured to assess whether there is indication of some improvement in the key areas the toolkit aims to target. Measures relating to children include *child dimensional psychopathology*, assessed using the teacher and parent-reported Strengths and Difficulties Questionnaire,^30^ and *child-reported satisfaction with school* using the How I Feel About My School measure.^36^
*Teacher well-being* will be measured using the Warwick‐Edinburgh Mental Wellbeing Scale 14-item Teacher Survey^37^ the Teachers’ Sense of Efficacy Scale,^38^ and the Relationship with Work Survey from the Maslach Burnout Inventory-General Survey,^39 40^ and the social skills and academic competence subscales from the SSIS will be completed by teachers. These will be collected at the beginning and end of the baseline period, at the end of the intervention term and at the end of the follow-up term. Other module-specific measures which are not covered by the above measures will be administered depending on the modules used by each child, for example, the Harter Self-Perception Profile for Children to measure self-esteem.^41^

Methods for collecting data on *healthcare and education resource use* and *health-related quality of life* will also be established and tested. Child quality of life (child-report and parent-proxy) will be measured using the Child Health Utility for Economic Evaluation (CHU9D).^42^ A tool to accurately capture education and healthcare resource use will be developed for the study, drawing on the Client Service Receipt Inventory^43^ and measures in the Database of Instruments for Resource Use Management Repository. Participants will complete this at baseline and follow-up, and provide qualitative information on changes in resource use during the follow-up process evaluation. A data collection form will also capture data on resource use and costs associated with the set-up and delivery of the intervention.

*Observational measures of child behaviour* in the classroom will also be tested throughout the study. These include but are not limited to the Classroom Observation Code,^44^ and the Teacher-Pupil Observation Tool.^45^ Observations will be carried out at school by members of the research team, trained to an acceptable reliability (0.7 or higher).

All data will be collected online via secure servers, or on paper, and manual data entry will be double checked.

### Analysis

#### Aim 1: To assess whether the toolkit is feasible and acceptable for schools to implement

We will use the definition of acceptability proposed by Sekhon *et al*^46^: ‘a multi-faceted construct that reflects the extent to which people delivering or receiving a healthcare intervention consider it to be appropriate, based on anticipated or experienced cognitive and emotional responses to the intervention’. Qualitative data from both the toolkit iteration interviews and the process evaluation interviews and focus groups will be audio recorded, transcribed and analysed using the Framework method and Thematic analysis.^47^ An initial coding framework will be developed after reading and re-reading transcripts. Deductive codes derived from the research questions and inductive codes within the data will be identified. This framework will be applied independently to three transcripts; discrepancies in coding will be discussed and revisions made to the framework which will then be applied to the remaining transcripts, with further discussion and revision where necessary.

Responses relating to each component of the toolkit will be synthesised in a framework in order to assess the acceptability of the evolving and final prototype; specifically to assess whether the components and the overall toolkit are considered appropriate to support children with ADHD in school. In addition, acceptability of the toolkit will be quantitatively assessed against the study progression criteria that relate to completion of each component of the toolkit, attendance at toolkit-related meetings, and the percentage of occasions the participant reports using the toolkit as instructed. The qualitative findings will be used to explain and further explore quantitative results in a mixed-methods synthesis. Modifications will be made iteratively as findings emerge, and by the end of the study each indicator should be in the ‘green’ range in order to indicate that the toolkit is acceptable.

